#### **4.4 Sample size calculation**

Per treatment group 44 per group (88 for both groups) is needed to achieve 81% power to detect a difference between the two treatment groups and the control group. The proportion in the Peg-IFN and adefovir group is assumed to be 0.01 under the null hypothesis and 0.20 under the alternative hypothesis. The proportion in the control group (no treatment) is 0.01. The test statistic used is the two-sided Fisher's Exact test. The significance level of the test was targeted at 0.05. A group sample of 44 persons in the control group is needed to achieve a 81% power to detect a difference between the Peg-IFN adefovir or Peg-IFN tenofovir.

Regarding a 10% drop-out due to Peg-IFN side-effects or other reasons a total of 50 patients are needed in each group.

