## 9 STATISTICAL ANALYSIS

### 9.1 Descriptive statistics

The main efficacy variable in the comparison of treatments A and B to treatment C ( no treatment) is the proportion of subjects in each treatment group achieving loss of HBsAg. The primary objective is to demonstrate superior efficacy of treatment A and/or B to treatment C.

The sample sizes were calculated as follows:

Per treatment group 44 per group (88 for both groups) is needed to achieve 81% power to detect a difference between the two treatment groups and the control group. The proportion in the PEG/IFN and adefovir group is assumed to be 0.01 under the null hypothesis and 0.20 under the alternative hypothesis. The proportion in the control group (no treatment) is 0.01. The statistical test used is the two-sided Fisher's Exact test . The significance level of the test was targeted at 0.05. A group sample of 44 persons in the control group is needed to achieve a 81% power to detect a difference between the PEG/IFN adefovir or PEG/IFN tenofovir.

Regarding a 10% drop-out due to peginterferon side-effects or other reasons a total of 50 patients are needed in each group.

Univariate logistic regression analyses will be performed to identify predictors of response to the combination therapy of PEGASYS® and ADF dipivoxil (Hepsera®) and PEGASYS® and tenofovir. Significant predictors from the univariate analysis will be combined into a multivariate logistic regression analysis. As a rule of thumb, the number of potential predictors to be included in a multivariate analysis should not exceed the number of responders (or non-responders, whichever is the lowest) divided by 10. With 100 patients included, the maximum number of predictors in a multivariate analysis is five, assuming a response rate of 0.50. Initially, the number of significant predictors from univariate analysis to be included in the multivariate analysis will be restricted following multi colinearity diagnostics. If the number of potential predictors remains too large however, a bootstrap procedure will be followed drawing 200 samples of the same size as the original (n=100) with replacement, each time repeating the multivariate logistic regression analysis. Descriptives of this bootstrap procedure will be reported to identify a stable predictor set. The level of significance during all these analyses is set at 0.05.

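### Cheap gain in power: Boschloo's exact test with Holm could replace the valid but conservative Fisher test for the two primary comparisons

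*Protocol*

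**What the plan says.** Section 4.4 sizes the trial on one regimen against no treatment: "The proportion in the Peg-IFN and adefovir group is assumed to be 0.01 under the null hypothesis and 0.20 under the alternative hypothesis", and "The proportion in the control group (no treatment) is 0.01". It fixes the test: "The test statistic used is the two-sided Fisher's Exact test". The level is 0.05 ("The significance level of the test was targeted at 0.05") and the result is "Per treatment group 44 per group (88 for both groups) is needed to achieve 81% power". An allowance for 10% drop-out brings enrolment to 50 per arm.

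Section 9.1 restates the calculation and the test: "The statistical test used is the two-sided Fisher's Exact test". It also sets the success criterion: "The primary objective is to demonstrate superior efficacy of treatment A and/or B to treatment C". There are thus two comparisons with one shared control arm, and either is enough for a claim. Section 9.2 names the same Fisher test for the interim analyses. The protocol gives no adjustment for the two comparisons; an analysis plan that is not shown may do so.

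**The concern.** Fisher's test conditions on the total number of responders. With about 44 to 50 patients per arm and very few expected control losses, the attainable p-values are coarse and the test spends well under its nominal 5%. An unconditional exact test can recover much of that slack while still keeping its size at or below 0.05 for every common rate.

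At stake is power that the trial could have from the same patients. It matters most for showing both regimens superior, and it would also let error control over the two comparisons be added at little cost.

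**Working it through.** **Inputs.** From section 4.4: 0.20 versus 0.01, two-sided 0.05, 44 evaluable and 50 enrolled per arm. From section 9.1: two comparisons, either sufficient. Assumed: tenofovir regimen also at 0.20. Section 4.4 gives a rate for the adefovir regimen only, but section 1 hypothesises a high rate of loss for both.

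**1. The plan's own figure.** Power is the sum, over all 45 × 45 tables, of the binomial probability at 0.20 times the binomial probability at 0.01, counting tables with two-sided Fisher p ≤ 0.05. Result: 0.8058, against the stated 81%. Drop-out: 44/(1 − 0.10) = 48.9, so 49; the plan has 50.

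**2. How conservative Fisher is.** The same sum with a common rate in both arms, maximised over that rate, gives 0.031 (44 per arm) and 0.035 (50 per arm). At a common rate of 0.01 it is about 0.00001.

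**3. Boschloo.** Its p-value is the maximum, over the common rate, of the probability that the two-sided Fisher p is no larger than the one observed. It orders tables as Fisher does, so at the same level it rejects every table that Fisher rejects. Its maximum size at 0.05 is 0.048 (44 per arm).

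Single comparison at 0.05, 20% versus 1%:

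| Per arm | Fisher | Boschloo |
|---|---|---|
| 44 | 80.6% | 88.0% |
| 50 | 87.1% | 92.6% |

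**4. Where the gain comes from (44 per arm).** For 5/44 versus 0/44, Fisher p = 2 × C(44,5)/C(88,5) = 2 × 1,086,008/39,175,752 = 0.055, not significant; Boschloo p = 0.042. For 7/44 versus 1/44, Fisher p = 0.058 and Boschloo p = 0.042. Under 20% versus 1% the first table has probability 0.0577 × 0.6426 = 0.0371 and the second 0.1273 × 0.2856 = 0.0364. Together they make 0.0735 of the 0.0747 gain.

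Both p-values pass 0.05 but not Holm's first step of 0.025. With no control losses, Fisher needs 6 treated losses at 0.05 (p = 0.026). Boschloo with Holm also needs 6 (p = 0.015), unless the other regimen has already passed.

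**5. Two comparisons with a shared control.** Holm tests the smaller p at 0.025, then the other at 0.05. Exact three-arm enumeration, 44 per arm, control 1%:

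| Procedure | Each | Both | At least one | If only one regimen works |
|---|---|---|---|---|
| Fisher, unadjusted | 80.6% | 66.7% | 94.4% | 80.6% |
| Fisher + Holm | 76.1% | 65.1% | 87.1% | 68.5% |
| Boschloo + Holm | 85.8% | 78.3% | 93.4% | 79.7% |

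The first three power columns put both regimens at 20%; the last puts the other regimen at 1%. At 50 per arm Boschloo + Holm gives 91.4%, 86.3%, 96.5% and 86.9%.

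**6. Sensitivity to the control rate.** If only one regimen works, unadjusted Fisher versus Boschloo + Holm at 44 per arm is 71.8% versus 69.4% at a control rate of 2%, and 63.1% versus 59.6% at 3%.

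**7. Family-wise error when neither regimen works.** The unadjusted Fisher pair reaches at most 0.057 (44 per arm) and 0.065 (50 per arm), at common rates of about 0.36 to 0.50. At 44 per arm it is about 0.00001 at a rate of 1%, 0.010 at 5% and 0.036 at 10%. Boschloo + Holm reaches at most 0.046 (44 per arm) and 0.045 (50 per arm).

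**The case against.** The strongest reply is that nothing in the plan is wrong. Fisher's test is valid, the 81% is right, and the choice of exact test is a preference. That stands, and it is why this is offered as an improvement.

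The reply goes further. Success is defined as either regimen, so at-least-one power is the plan's own measure, and there the proposal is one point lower. A reader might infer from the 66.7% for both regimens that the trial is underpowered for its objective. The protocol does not require both, so that does not follow.

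A reader might also infer that the current plan inflates the error over two comparisons. The excess over 0.05 appears only at loss rates far above anything assumed for untreated patients; at 1% it is negligible.

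Nor does the gain fully pay for Holm. Boschloo's dominance over Fisher holds at equal level. At Holm's first step it is no longer guaranteed, and the loss when only one regimen works grows with the control rate. Section 1 puts spontaneous loss at 1–2% per year in Western patients, so rates of 2–3% over the study are not remote.

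What survives is this. At equal error control, Boschloo with Holm beat Fisher with Holm in every scenario computed. Against the unadjusted plan it gains clearly per comparison and for both regimens when both work, and gives up little otherwise.

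**Conclusion.** A worthwhile, low-cost improvement to a valid plan. On the protocol's own inputs and 44 per arm, changing the test alone adds 88.0 − 80.6 = 7.4 points to a single comparison. With Holm added and both regimens at 20%, the net gain is 85.8 − 80.6 = 5.2 points per comparison and 78.3 − 66.7 = 11.6 points for both, with family-wise error when neither regimen works of at most 0.046.

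The costs are 1.0 point of at-least-one power, and, if only one regimen works, 0.9 point at a control rate of 1%, 2.4 at 2% and 3.5 at 3%.

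The two-regimen figures rest on the assumed 20% for tenofovir. All figures are for a single analysis: Holm covers the two comparisons and not the repeated looks in section 9.2.

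**What to change.** Before any outcome data are seen, and so before the first look at 50 patients in this open-label trial:

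- In 4.4 and 9.1, name the two-sided Boschloo unconditional exact test, with the two-sided Fisher p-value as its statistic, for each regimen against no treatment, with Holm over the two comparisons at an overall 0.05.
- Restate the power from that procedure, with the assumed tenofovir rate and the downsides above.
- In 9.2, name the same test, and handle the repeated looks separately.
- Keep Fisher's test as a sensitivity analysis.

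State how the p-value is computed. For 5/44 versus 0/44 the SciPy routine returns 0.042 with the arms as columns, which matches the enumeration, but 0.025 with the arms as rows.

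The cost is amended wording in three sections, notified as section 11.2 requires, standard software, and a test that is less familiar to clinical readers. No extra patients, visits or data are needed.

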## **5. TREATMENT OF SUBJECT**

### **5.1 Investigational product/treatment**

Peginterferon alfa-2a (40KD) (PEGASYS®) + Adefovir (ADF) dipivoxil (Hepsera®)

Peginterferon alfa-2a (40KD) (PEGASYS®) + Tenofovir (TDF) disoproxil fumarate (Viread®)

### **5.2 Use of co-intervention**

All medication (prescription and over-the-counter) administered from signing of informed consent onwards until the safety follow-up visit should be recorded in the CRF.

When having heterosexual intercourse, female subjects of childbearing potential and non-vasectomized male subjects who have a female partner of childbearing potential must use a combination of 2 effective birth control methods during dosing with Peg-IFN and TDF or ADF and for 6 months after discontinuation of therapy.

Use of co-intervention (e.g. painkillers) will be to the discretion of the investigator

### **5.3 Escape medication**

Use of escape medication (e.g. switch of antiviral therapy due to side effects) will be to the discretion of the investigator.

## 6. INVESTIGATIONAL MEDICINAL PRODUCT

### 6.1. Name and description of investigational medicinal product

### 6.2. Product Information

#### **Peginterferon alfa-2a (40KD) (PEGASYS®)**

##### Summary of findings from non-clinical and clinical studies

Peginterferon alfa-2a (40KD) (PEGASYS®) was developed through the process of pegylation, whereby a large, 40-kDa, branched-chain polyethylene glycol (PEG) molecule is attached to the base interferon alfa-2a molecule to produce a drug with a prolonged half-life. The size of the PEG molecule and its structure are factors affecting the pharmacokinetic properties of pegylated interferons. The attachment of a 40-KD, branched PEG moiety to interferon alfa-2a results in a drug with a once weekly frequency of administration which maintains effective concentrations of peginterferon alfa-2a (40KD) throughout the dosing interval while substantially reducing the peak-to-trough ratio. Hence, sharp increases to peak serum concentrations can be avoided, which are linked to a number of adverse events associated with thrice-weekly IFN $\alpha$  dosing.(35)

PEGASYS®, as monotherapy and in combination with ribavirin has been approved for use in patients with chronic hepatitis C (36).

PEGASYS® was recently approved in the EU for treatment of HBeAg positive as well as HBeAg-negative chronic hepatitis B. The clinical development of PEGASYS® for chronic hepatitis B consists of a phase II study in patients with HBeAg-positive HBV (37) and two pivotal phase III trials in HBeAg-positive and HBeAg-negative disease (38). The HBeAg-positive study results were presented in 2004.

The primary aim of the phase II study was to compare the efficacy and safety of PEGASYS® administered once weekly for 24 weeks at 90  $\mu$ g, 180  $\mu$ g and 270  $\mu$ g with conventional IFN $\alpha$ -2a 4.5 MIU thrice weekly in patients with HBeAg-positive chronic hepatitis B.

A total of 194 adult patients were enrolled in this randomized, open-label, multicenter study. Included patients were IFN $\alpha$  naïve and had received less than 6 months treatment with nucleoside/nucleotide analogues and/or had not received nucleoside/nucleotide therapy in the 6 months prior to the study. Patients with decompensated cirrhosis were excluded. All patients were serum positive for HBeAg, HBsAg and had viral loads >500,000 HBV DNA cop/mL. Chronic hepatitis B status was confirmed by liver biopsy and, at the time of screening, all patients had baseline ALAT levels over 2-fold greater but <10 x ULN. Patients

were randomized to four treatment arms and treated for 24 weeks with either conventional IFN $\alpha$ -2a or with one of three doses of PEGASYS®. All patients were monitored for an additional treatment-free 24-week follow-up period.

The percentages of patients achieving a combined response (HBeAg loss, HBV DNA <500,000 cop/mL, ALAT normalization) at end-of-follow-up (week 48) were 12%, 27%, 28% and 19% for conventional IFN $\alpha$ -2a, PEGASYS® 90  $\mu$ g, 180  $\mu$ g and 270  $\mu$ g once weekly, respectively. When the data from all PEGASYS® doses were pooled, the combined response rate was 24% and this was statistically significantly different compared with conventional IFN $\alpha$ -2a ( $P=0.036$ ). In terms of on-treatment HBV DNA suppression, a PEGASYS® dose of 180  $\mu$ g gave a greater response at the end of week 24. At week 24, HBV DNA levels had not yet reached a plateau but continued to decline (37). Of the patients treated with 180  $\mu$ g PEGASYS® 33% had HBeAg seroconversion and 35% had HBeAg loss after 24 weeks of treatment and 24 weeks follow-up.

Advantages of PEGASYS® over interferon alfa-2a were noted also in the subgroups of patients with difficult-to-treat disease such as those with liver cirrhosis, low ALT, and/or high HBV DNA at baseline as well as patients with HBV genotype C (37).

Overall, the data from this phase II study demonstrates that PEGASYS® has substantially higher efficacy than conventional IFN $\alpha$ -2a in patients with HBeAg-positive CHB .

Two phase III, randomized clinical trials with PEGASYS® in chronic hepatitis B have been performed. These trials investigated the potential of PEGASYS® (180 mcg once weekly) alone and in combination with lamivudine (100 mg daily) in the treatment of HBeAg-positive and HBeAg-negative CHB. A treatment duration of 48 weeks was proposed for the phase III trials as a result of the phase II data, which demonstrated a continuing decline in HBV DNA levels at week 24.

The principal objective of the first phase III study was to compare the efficacy and safety of PEGASYS® 180  $\mu$ g once weekly with and without lamivudine 100 mg daily, to that of lamivudine 100 mg daily in the treatment of HBeAg-positive patients with CHB. A total of 814 adult patients have been enrolled and they have been randomized to one of the three treatment arms receiving 48 weeks of anti-viral therapy and monitored for a further 24 weeks post-treatment. At end of follow-up HbeAg seroconversion and HBV-DNA < 100,000 cop/mL was observed in 32 % of patients treated with Pegasys® with placebo ( $p<0.001$ ), 27 % ( $p<0.023$ ) with Pegasys® and Lamivudine and 19 % with Lamivudine alone. Also HbeAg loss and ALT normalization was significantly higher in 2 groups treated with Pegasys® than in the group with Lamivudine alone (38).

The aim of the second phase III study was to compare the efficacy and safety of PEGASYS® 180 µg once weekly with and without lamivudine 100 mg daily, to that of lamivudine 100 mg daily in the treatment of HBeAg-negative patients with CHB. The 537 adult patients in this trial have been randomized to one of the three treatment arms. All patients have received 48 weeks of anti-viral treatment and have been monitored for a further 24 weeks post-treatment period.

After 24 weeks of follow-up, the percentage of patients with normalization of alanine aminotransferase levels or hepatitis B virus (HBV) DNA levels below 20,000 IU/mL was significantly higher with peginterferon alfa-2a monotherapy (59 % and 43 % respectively) and peginterferon alfa-2a plus lamivudine (60 % and 44 %) than with lamivudine monotherapy (44 %,  $P=0.004$  and  $P=0.003$  respectively; and 29 %,  $P=0.007$  and  $P=0.003$  respectively). At the end of follow-up rates of sustained suppression of HBV DNA to below 400 copies per milliliter were 19 % with peginterferon alfa-2a monotherapy, 20 % with combination therapy and 7 % with lamivudine alone ( $P<0.001$  for both comparisons with lamivudine alone). Loss of hepatitis B surface antigen occurred in 12 patients in the peginterferon groups, as compared with 0 patients in the group given lamivudine alone.

At end of follow-up (week 72), using the intent to treat analysis, the percentage with normalised ALAT or HBV-DNA ( $< 20,000$  cop/mL) was significantly higher in the PEGASYS® plus placebo and PEGASYS® plus lamivudine groups than in the lamivudine group (38) .

In multivariate analyses, high ALT, low HBV-DNA and low HBeAg levels at baseline were significant predictors of HBeAg seroconversion ( $P< 0.001$ ). In HBeAg-positive CHB, marked ALT flares during INF-based treatment have been associated with HBeAg seroconversion and viral suppression. Marked on-treatment ALT elevations were generally more frequent with peginterferon alfa-2a monotherapy and were more common in patients with HBeAg seroconversion 24 weeks after the end of treatment (37, 39).

#### Summary of known and potential risks and benefits

PEGASYS can cause a broad variety of serious adverse reactions . The most common life-threatening or fatal events induced or aggravated by PEGASYS were depression, suicide, relapse of drug abuse/overdose, and bacterial infections, each occurring at a frequency of  $< 1\%$ . Hepatic decompensation occurred in 2% (10/574) of CHC/HIV patients .

In clinical trials of 48 week treatment duration, the adverse event profile of PEGASYS® in chronic hepatitis B was similar to that seen in chronic hepatitis C PEGASYS® monotherapy

use, except for exacerbations of hepatitis. Six percent of PEGASYS® treated patients in the hepatitis B studies experienced one or more serious adverse events.

The most common or important serious adverse events in the hepatitis B studies were infections (sepsis, appendicitis, tuberculosis, influenza), hepatitis B flares, anaphylactic shock, thrombotic thrombocytopenic purpura.

The most commonly observed adverse reactions were pyrexia (54% vs. 4%), headache (27% vs. 9%), fatigue (24% vs. 10%), myalgia (26% vs. 4%), alopecia (18% vs. 2%), and anorexia (16% vs. 3%) in the PEGASYS and lamivudine groups respectively.

Overall 5% of hepatitis B patients discontinued PEGASYS therapy and 40% of patients required modification of PEGASYS dose. The most common reason for dose modification in patients receiving PEGASYS therapy was for laboratory abnormalities including neutropenia (20%), thrombocytopenia (13%), and ALT disorders (11%).

#### Description and justification of route of administration and dosage

The recommended dose of PEGASYS monotherapy for hepatitis B is 180 µg (1.0 mL vial or 0.5 mL prefilled syringe) once weekly for 48 weeks by subcutaneous administration in the abdomen or thigh.

When dose modification is required for moderate to severe adverse reactions (clinical and/or laboratory), initial dose reduction to 135 µg (which is 0.75 mL for the vials or adjustment to the corresponding graduation mark for the syringes) is generally adequate. However, in some cases, dose reduction to 90 µg (which is 0.5 mL for the vials or adjustment to the corresponding graduation mark for the syringes) may be needed. Following improvement of the adverse reaction, re-escalation of the dose may be considered

#### Dosages, dosage modifications and method of administration

##### Hematological:

Dose reduction from 180µg to 135µg is required if absolute neutrophil counts are < 750/mm^3. If ANC < 500/mm^3, treatment should be suspended until ANC values return to more than 1000/mm^3. Treatment must be reinstituted at 90 µg and monitor ANC needs to be monitored. When platelet counts are < 50,000/mm^3, dosage must be reduced to 90 µg. Treatment must be discontinued if platelet count < 25,000/mm^3.

##### Psychiatric

Dose reduction from 180µg to 135µg is required in cases of moderate depression. Treatment should be discontinued in severe depression.

### Renal Function

In patients with end-stage renal disease requiring hemodialysis, dose reduction to 135 µg PEGASYS is recommended. Signs and symptoms of interferon toxicity should be closely monitored.

### Liver Function

If ALT increases are progressive despite dose reduction or accompanied by increased bilirubin or evidence of hepatic decompensation, therapy should be immediately discontinued.

In chronic hepatitis C patients with progressive ALT increases above baseline values, the dose of PEGASYS should be reduced to 135 µg and more frequent monitoring of liver function should be performed. After PEGASYS dose reduction or withholding, therapy can be resumed after ALT flares subside.

In chronic hepatitis B patients with elevations in ALT ( $> 5 \times \text{ULN}$ ), more frequent monitoring of liver function should be performed and consideration should be given to either reducing the dose of PEGASYS to 135 µg or temporarily discontinuing treatment. After PEGASYS dose reduction or withholding, therapy can be resumed after ALT flares subside.

In patients with persistent, severe (ALT  $> 10$  times above the upper limit of normal) hepatitis B flares, consideration should be given to discontinuation of treatment. (35).

### **Adefovir (ADF) dipivoxil (Hepsera®)**

#### Summary of findings from non-clinical and clinical studies

Adefovir (ADF) dipivoxil (Hepsera®) is a synthetic adenine nucleotide analogue that has recently been licensed for the treatment of CHB in the United States and Europe.

In vitro, the concentration of adefovir required to inhibit 50% of HBV DNA synthesis ranged from 0.2-2.5 µmol/L in a variety of HBV DNA-producing human hepatoma cell lines. Additive antiviral effects were observed when adefovir was combined with lamivudine, or with one of the experimental drugs entecavir or telbivudine.

Large, placebo-controlled clinical trials have shown potent activity against HBV in both HBeAg-positive and HBeAg-negative patients that is associated with significant biochemical, virologic, and histologic improvement. Moreover, resistance to this agent has not been observed in up to 48 weeks of therapy. The drug has been shown to be effective both in wild-type and lamivudine-resistant forms of HBV both in vitro and in vivo. Clinical trials to date

show that virologic and biochemical improvement are observed after adefovir dipivoxil is added to ongoing lamivudine therapy in lamivudine-resistant patients or when adefovir dipivoxil is administered as monotherapy (15, 16, 40). In HBeAg positive chronic hepatitis B patients (n=515) ADF given in dosages of 10 mg, 30 mg or placebo per day for 48 weeks showed that after 48 weeks of treatment, significantly more patients who received 10 mg or 30 mg of ADF dipivoxil per day than who received placebo had histologic improvement (53 percent [P<0.001], 59 percent [P<0.001], and 25 percent, respectively), a reduction in serum HBV DNA levels (by a median of 3.52 [P<0.001], 4.76 [P<0.001], and 0.55 log cop/mL, respectively), undetectable levels (fewer than 400 cop/mL) of serum HBV DNA (21 percent [P<0.001], 39 percent [P<0.001], and 0 percent, respectively), normalization of ALAT levels (48 percent [P<0.001], 55 percent [P<0.001], and 16 percent, respectively), and HBeAg seroconversion (12 percent [P=0.0491], 14 percent [P=0.01], and 6 percent, respectively). No ADF-associated resistance mutations were identified in the HBV DNA polymerase gene. The safety profile of the 10-mg dose of ADF dipivoxil was similar to that of placebo; however, there was a higher frequency of adverse events and renal laboratory abnormalities in the group given 30 mg of ADF dipivoxil per day (15).

In HBeAg negative CHB patients (n=185) ADF given in a dosage of 10 mg or placebo once daily for 48 weeks shows that at week 48, 64 percent of patients who had base-line liver-biopsy specimens available in the ADF dipivoxil group had improvement in histologic liver abnormalities (77 of 121), as compared with 33 percent of patients in the placebo group (19 of 57, p<0.001). Serum hepatitis B virus (HBV) DNA levels were reduced to fewer than 400 cop/mL in 51 percent of patients in the ADF dipivoxil group (63 of 123) and in 0 percent of those in the placebo group 0 of 61, p<0.001). The median decrease in log-transformed HBV DNA levels was greater with ADF dipivoxil treatment than with placebo (3.91 vs. 1.35 log cop/mL, P<0.001). ALAT levels had normalized at week 48 in 72 percent of patients receiving ADF dipivoxil (84 of 116), as compared with 29 percent of those receiving placebo (17 of 59, P<0.001). No HBV polymerase mutations associated with resistance to ADF were identified. The safety profile of ADF dipivoxil was similar to that of placebo (16).

Follow-up results after 48 weeks of treatment with 10 mg AFD were presented at the ISVHLD 2003 meeting in Sydney [45]. At the end of 24 weeks follow-up without treatment, 5 % of the ADF group had undetectable HBV-DNA levels (HBV-DNA < 1000 cop/mL). After 48 weeks of follow-up 8% had undetectable HBV-DNA levels (HBV-DNA < 1000 cop/mL).

Two studies (40, 41) showed that in chronic hepatitis B with compensated and decompensated liver disease due to YMDD related Lamivudine resistance, ADF 10 mg once daily given for 48-52 weeks resulted in a significant virological and biochemical improvement.

